
We will monitor if participants adhere to all the sessions offered for counselling and in case of non-adherence or failure to engage in counselling, the counsellor will follow specific protocol to encourage reengagement. In Spain, the psychologist will contact the woman two to three times through the preferred mean (email or phone). In Denmark, a project midwife will try to contact the woman on the preferred mean (email or phone) at 3 occasions within 6 weeks. The content of the six individually tailored sessions will be based on the Dutton’s Empowerment Model [27] and the Psychosocial Readiness Model [28]. Specifically, the contents will include (session 1) the evaluation of abusive behaviour (which will also served to protect the pregnant women is the level of violence detected is high); (session 2) safety planning, network and resources; (session 3) psycho-education (healthy relationships, cycle of violence…); (session 4) self-esteem and self-care and (sessions 5 & 6) empowerment, choice making and problem solving. The video consultations will be planned for every 2 weeks at a time where the women feel comfortable. However, schedule flexibility will always prevail to promote women participation. Criteria for discontinuing or modifying allocated interventions will be applied to women with an elevated risk for IPV who will be routinely treated according to the standard protocol in each country. In other words, if during the interventions the health providers detect an increased on the level of violence, they will apply the established national protocols to protect the pregnant women.

Control group: IPV positive women who accept the e-Health intervention package will be asked for a second consent to receive a delayed intervention (8 weeks later) and to complete the baseline and outcome measurements. Women can request to leave the control group at any time and receive the intervention immediately (in which case the data will be part of the cohort study).

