### Protecting participants and safety reporting

By taking part in the study, participants will automatically enter a project where a greater level of care will become available to them. The study has well-established security protocols. The screening questionnaires will capture the severity of violence permitting us to refer women at high risk of danger to the relevant national authorities responsible their protection. During of the first videocounselling session, even if the questionnaires did not register a high level of risk, the danger to the life of the participants will be specifically evaluated. If a risk of danger is detected, the same protocol as above will be applied. All the videocounselling sessions will be carried out with a high level of vigilance concerning danger. It should be noted that the intervention itself (as explain above) contains features that are protective, for example, a link that expiries after the counseling sessions, a protection plan back by easy-to-use features to activate emergency contacts, camouflage of the app and emergency exit button. The videocounselling providers will receive in-session protection training, for example, to change the topic of the conversation in case the partner shows up unexpectedly during the sessions. Videoconsellors and women will talk about these options at the beginning of the intervention; in this way both will know what to do if something like this happens.

For safety reporting, if severe or life-threatening abuse of a pregnant woman is identified by the IPV counsellors, the principal investigator will be notified and the woman will be treated according to the standard protocol in each country. The study does not add any risk or harm for the women, we will therefore not provide a post-trial care for compensation. On the contrary, it is anticipated that video counselling addressing safety behavior and safety planning has the potential to increase safe behaviors and thus decrease IPV exposure. We also anticipate that the participating midwives will experience a greater competence and confidence in approaching the topic of violence and handling women who are exposed to IPV. Women will benefit from health professionals who enquire in an appropriate way about violence. In addition, information will be provided about IPV community resources which the women may make use of after the e-health intervention is finished.

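### The danger-to-life evaluation meant for women the questionnaires miss sits in video session 1, so allocation to control postpones it by eight weeks, and the escalation rule is not clearly worded to cover the wait

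*Protocol article*

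**What the plan says.** All references are to the protocol article.

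- **Before randomisation (Eligibility criteria; Study interventions and assessments).** Providers look at the ISA physical items and the items on fear of the partner. Women positive on these are assessed with the EPV-R. If danger is confirmed as high, they are not included and go to the national standard pathway. This applies before allocation and is the same for everyone.
- **Session 1 (Protecting participants and safety reporting).** "During of the first videocounselling session, even if the questionnaires did not register a high level of risk", the text continues, "the danger to the life of the participants will be specifically evaluated". The session list under Study interventions and assessments likewise gives session 1 a protective purpose.
- **Later sessions (same safety section).** "All the videocounselling sessions will be carried out with a high level of vigilance concerning danger".
- **Escalation (Study interventions and assessments).** "if during the interventions the health providers detect an increased on the level of violence, they will apply the established national protocols".
- **Control group (same section; also Trial design).** Control women are approached again after allocation and "will be asked for a second consent to receive a delayed intervention (8 weeks later"). They complete baseline and outcome measurements. "Women can request to leave the control group at any time and receive the intervention immediately".
- **Duties not tied to one group.** Under concomitant care, counsellors record whether women in either group need community resources, and standard care stays open to both. Under safety reporting, "if severe or life-threatening abuse of a pregnant woman is identified by the IPV counsellors, the principal investigator will be notified".
- **Overall statement on risk.** "The study does not add any risk or harm for the women".

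**The concern.** The plan does not treat the questionnaires as sufficient. It adds a face-to-face evaluation by video precisely for women whose answers did not show high risk. That second check is part of the package, and the package is what control women wait for. A control woman whose danger was missed at entry is therefore due this check eight weeks later than she would have been in the other group, for no reason except her allocation.

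The women concerned have already screened positive for partner violence and accepted help. At stake is the safety of the control group during the wait, and the accuracy of the statement that the study adds no risk. The same arrangement could also be carried into the full-scale trial, since the article says that the length of its delay will be set partly from what the pilot observes.

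**Working it through.** The plan gives no figure to reproduce. The check sets the two groups side by side, with a small amount of arithmetic.

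| Time | Intervention group | Control group |
|---|---|---|
| Before randomisation | ISA items, EPV-R if positive, exclusion if danger is high | The same |
| After allocation | Session 1, with danger-to-life evaluation | Second-consent contact; the text attaches no danger evaluation to it |
| Next eight weeks | Further sessions, each with vigilance for danger | Wait; exit on request, standard care, unscheduled counsellor duties |
| End of delay | Sessions continue | Session 1, with danger-to-life evaluation |

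**Length of the gap.** Let session 1 take place *s* weeks after a woman is due to start. The intervention group is evaluated at week *s* and the control group at week 8 + *s*. The difference is (8 + *s*) − *s* = 8 weeks, whatever *s* is, provided that it is similar in both groups. Sessions are planned every two weeks, so the delay spans 8 / 2 = 4 session intervals. The article allows flexible scheduling, so this is the planned spacing, not a guaranteed one.

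**Number of women.** There are 5 control women per country in 2 countries: 5 × 2 = 10. Women who decline the delay stay in the cohort, receive the package and are replaced, so the gap applies to those who accept.

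**Does another planned step close the gap?**

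1. *The EPV-R.* It is given before randomisation, and only to women positive on the ISA items. Session 1 is aimed at those it does not reach.
2. *The second-consent contact.* This is a planned contact with every control woman. Its described content is information and consent to the delay.
3. *The outcome questionnaires.* They include the ISA, but Recruitment: Consent procedures times them at one month after the intervention. The text neither places one within the wait nor links one to a danger evaluation.
4. *The escalation rule.* The sentence before it is general: it refers to modifying or stopping allocated interventions in women at elevated risk. The next sentence restates it as applying during the interventions. A woman still waiting is not clearly covered.
5. *The reporting rule and the record of needs.* Neither is restricted to one group, but the text gives no contact, time point or danger tool for either during the wait.

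None of the five is described as supplying the session 1 evaluation before the delay ends.

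**The no-risk sentence.** Compared with usual care, it can be defended: control women keep standard care and later receive the package. Compared with the immediate package that the rest of the cohort receives, it is too broad, because one safety evaluation is postponed.

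**The case against.** The strongest reply is that this is an argument from silence. The article is condensed, the schedule (Fig 1) and the flowchart (Fig 2) are not shown, and the text refers to established security protocols and national pathways. A check during the wait may exist. That limits the point to the readable text. But the text does more than stay silent: it places the evaluation in session 1 and delays session 1.

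It can also be said that delayed content is inherent in a delayed-intervention control. Survivors preferred this design, ethics committees approved it, and women give second consent and may leave at once. That stands as a defence of delaying the counselling. It does not require delaying a danger evaluation, which can be separated from the counselling.

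Some stronger readings are tempting and not supported:

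- *Control women have no planned staff contact.* They do: the second-consent approach.
- *Control women are unprotected.* They have the check before randomisation, exit on request, standard care, and counsellor duties that cover both groups.
- *Needs in the two groups cannot be compared, or the safety of the delay goes unobserved.* Counsellors record needs in both groups, interviews may take place at any point in the flow with safety as a named domain, and an advisory board reviews safety.
- *A probability that some control woman is in undetected danger can be stated.* The documents give no rate of missed danger, so any such figure would reflect only the rate assumed.

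**Conclusion.** The concern holds in limited form. As written, allocation to control postpones the danger-to-life evaluation by eight weeks for each of 10 planned women. The described safeguards during that time depend on the woman's own action or on counsellor duties without a stated schedule. The escalation rule is worded too narrowly, and the no-risk sentence lacks a comparator.

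This should be corrected for participant safety. It is not a claim that harm will occur, and it has no bearing on the stop-go criteria in Table 1. It assumes a similar lag to session 1 in both groups and that Figs 1 and 2 show no danger evaluation in the wait. If they do show one, the rewording of the escalation rule and of the no-risk sentence would still be worthwhile.

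**What to change.** 1. Do the danger-to-life part of session 1, without the counselling, in every woman before randomisation. Allocation then cannot delay it, and women found to be at high danger leave before allocation in both groups. If this is not feasible, do it in control women at the existing second-consent contact.
2. Reword the escalation rule so that it applies at any time after randomisation, the eight-week delay included, whenever staff detect high danger or rising violence.
3. Qualify the no-risk sentence: state that the comparison is with usual care, and that control women receive the package eight weeks later than the rest of the cohort.

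**Cost.** 20 short assessments by existing staff for the planned sample, plus one for each further woman assessed and then excluded or replaced; or 10 if done only in control women who accept the delay. For intervention women, the work is moved earlier rather than added. The control group receives a small co-intervention. The delayed-control design and the stop-go rules are unchanged.

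A brief check at about week 4 of the wait is optional. It adds a contact, with some confidentiality risk and further co-intervention, and is not part of the required change.

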### Objective

The objective is to assess the need and feasibility of randomising a sufficiently large number of women exposed to IPV during pregnancy in a full-scale future randomised trial. To achieve this, we will:

estimate rates of consent to randomization, and the rates of adherence and dropout following randomization (for the use in sample size estimation)determine recruitment durationexamine the women’s perception about the benefit of the interventiondetermine the reasons for acceptability, non-adherence, and obstacles to recruitment, randomisation and consent through qualitative interviews

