### Eligibility criteria

All women who fulfil the inclusion criteria will be screened and invited to receive an e-health package. Of those who accept the e-health intervention, 20 women will be randomised, 10 women in each country. In Spain and Denmark, respectively, 5 will be allocated in the intervention group and 5 will be asked to consent to be in the control group.

Inclusion criteria: pregnant women at <12 weeks gestation, who screen positive in IPV at the first antenatal visit and accept the e-health package.

Exclusion criteria: (1) women who cannot be informed about the study without their partners or other family members knowing; (2) mentally or physically incapacity to participate in the study; (3) women below 16 years in Spain or below 18 years in Denmark; (4) inability to understand Danish/Spanish, (5) lack of internet and electronic device and (6) women with extreme severity of IPV. Women selected to participate in the trial in this situation will receive an evaluation of danger before randomisation. If the severity of IPV is confirmed to be at high level of danger, these pregnant women will be routinely treated and supported according to the standard protocol in each country. Following this path, any potential risk for the women will be taken into account from the beginning of the process and women will be protected. Women who have same-sex partners will be screened, but their data will not be used for the purpose of this study.

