### Randomisation procedures

The research team will consult the data server on a daily basis to identify women who screen positive in IPV and accept to receive the e-health package to randomly allocate them (using a computer-generated random numbers) in the intervention or control group through randomisation at a ratio of 1:1. IPV counsellors will be informed of the assignments to each group. Women in the intervention group will be blinded but not women in the control group.

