Relevant concomitant care and interventions that are permitted during the trial: Women in both the intervention and control groups would be able to benefit from the standard care available for women exposed to IPV thorough the usual provision made by social and health services at any time during the study, if necessary. Indeed, one of the video-counselling sessions will be dedicated to inform women about the available resources in their community. IPV counsellors will specify if women in the intervention and the control group are in need of these resources during the time of the pilot as a valuable information for the future full-scale trial.

To accomplish the objectives, we will collect the following information:

Primary outcome:

Number of IPV positive women, who consented to receive e-health package and consented to randomization in the control group computed as a rate.

Secondary outcomes:

Number of women who consented to receive e-health package computed as a rate.Number of women in the intervention group where complete outcome data were obtained computed as a rate.Number of women in the control group where complete outcome data were obtained computed as a rate.Number of women where there was a study protocol violation computed as a rate.Recruitment duration (in days) to get the pilot sample (5 women for the intervention group and 5 women for the control group, in each country).Benefit of the intervention perceived by women through the information obtained in qualitative interviews.Perception about the duration of delay (the duration in the future full-scale trial will be determine according to the observations derived of the pilot study and the information provided in the qualitative interviews).Reasons for acceptability, non-adherence, and obstacles to recruitment, randomisation, consent and follow-up (through qualitative interviews).

Participant timeline

The participant timeline is illustrated in Fig 1.

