#### Progression criteria

Table 1 outlines the main criteria that will be considered to assess the feasibility of a full-scale RCT. In addition, our qualitative findings will also be used to support the decision-making around progression to a full-scale trial. For example, if a progression criterion outlined in Table 1 does not meet the threshold for progression, but we have developed a qualitative understanding of why this occurred and how it could be improved, then it may still be possible to proceed with the full trial. The research team of the STOP project will have access to these interim results.

**Table 1 pone.0282997.t001:** Suggested progression criteria in eIPV trial.

Feasibility objectives and related data to be collected	Go criteria to proceed to full trial	Criteria to reassess and adjust full trial protocol	Stop criteria
Study population			
1. Consent rate of eligible women	Rate >25% of eligible women agreeing to participate.	Rate between 11% and 24% women agreeing to participate	Rate <10% of eligible women agreeing to participate
Study outcomes			
2. Proportion of women in either intervention or control group for whom the allocated treatment is adhered to.	Adherence to allocated treatment in >80% of study sample.	Adherence to allocated treatment in between 51% and 79% of study sample.	Adherence to allocated treatment in <50% of study sample.
RCT process			
3. Collection of data on clinical outcomes	Complete data available of >80% of study sample.	Missing data between 21% and 49% of study sample.	Data missing of >50% of study sample.

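### Controls who leave the delay early are moved to the cohort, so criterion 2 can read Go when adherence among all randomised women is 80% or lower

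*Protocol article*

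**What the plan says.** All references are to the protocol article.

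- **Study interventions and assessments, control group.** A woman who no longer wishes to wait may ask to stop being a control, and would then "receive the intervention immediately (in which case the data will be part of the cohort study"). The control allocation is an eight-week wait before the package.
- **Progression criteria, Table 1, criterion 2.** The measure is "Proportion of women in either intervention or control group for whom the allocated treatment is adhered to". Go requires more than 80% of the study sample, reassessment covers 51% to 79%, and Stop is below 50%. The term study sample is not defined.
- **Secondary outcomes.** One is "Number of women in the control group where complete outcome data were obtained computed as a rate".
- **Objective.** The pilot is to estimate "the rates of adherence and dropout following randomization (for the use in sample size estimation").
- **Eligibility criteria.** "Of those who accept the e-health intervention, 20 women will be randomised, 10 women in each country". In each country, "5 will be allocated in the intervention group and 5 will be asked to consent to be in the control group".
- **Trial design.** Women who refuse the second consent stay in the cohort and are substituted until each country has its five controls. Nothing is said about replacing a control who crosses over later.

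**The concern.** A control adheres to her allocation, first of all, by waiting. Starting the package early is the characteristic failure of that allocation, and it is the one failure whose data the plan sends elsewhere. A woman who has left the control group and whose data sit in the cohort is, on plain words, no longer among the women whom criterion 2 or the control completeness rate counts. The Trial design section uses cohort status in the same way for women who refuse the second consent: they are outside the control sample.

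Other failures are treated differently. Data up to a withdrawal of consent are kept, and failure to obtain data is itself an outcome. No crossover rate appears among the listed outcomes to recover what is moved.

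Two things are at stake. The adherence criterion could pass because women who did not accept the wait were taken out of it. The full trial could also be sized with a dropout figure that omits crossover.

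**Working it through.** **Inputs from the article.** Two countries with 5 + 5 women each; allocation "in the intervention or control group through randomisation at a ratio of 1:1"; Go above 80%. The planned number reproduces: 2 × (5 + 5) = 20, that is 10 intervention women and 10 controls who gave the second consent. With 20 in the denominator, 16/20 is exactly 80% and is not Go, so Go needs at least 17.

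**Inputs assumed.** The article gives no crossover or adherence rates. The ranges used are crossover 10% to 50%, intervention adherence 70% to 90%, and adherence of the remaining controls 80% or 100%.

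**Formulas.** Let *a* be the number of adherent intervention women out of 10 and *x* the number of controls who cross over, with the remaining controls fully adherent.

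- All randomised, crossovers non-adherent: (*a* + 10 − *x*)/20
- Crossovers removed: (*a* + 10 − *x*)/(20 − *x*)

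**Results for *a* = 8.**

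| Crossovers | All randomised | Crossovers removed |
|---|---|---|
| 1 | 17/20 = 85%, Go | 17/19 = 89.5%, Go |
| 2 | 16/20 = 80%, not Go | 16/18 = 88.9%, Go |
| 3 | 15/20 = 75%, reassess | 15/17 = 88.2%, Go |
| 4 | 14/20 = 70%, reassess | 14/16 = 87.5%, Go |

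(Exactly 80% falls between the Go and reassess bands of Table 1.)

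**Other values of *a*.** The reading changes from not-Go to Go as follows.

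- 10/10 adherent: from 4 crossovers (16/20 = 80% against 16/16 = 100%).
- 9/10 adherent: from 3 crossovers (16/20 = 80% against 16/17 = 94.1%).
- 7/10 adherent: from 1 to 4 crossovers (with 1, 16/20 = 80% against 16/19 = 84.2%).
- 6/10 adherent: never, because even with no crossover the rate is 16/20 = 80%, and removing crossovers only lowers it (15/19 = 78.9% with 1).

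**Chance of Go.** Take *a* as binomial (10, intervention adherence), *x* as binomial (10, crossover rate), and adherent remaining controls as binomial (10 − *x*, their adherence). Sum the exact probabilities of all outcomes above 80%. At 80% intervention adherence and 30% crossover:

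| Adherence of remaining controls | True pooled adherence | P(Go), all randomised | P(Go), crossovers removed |
|---|---|---|---|
| 100% | (0.80 + 0.70 × 1.00)/2 = 75% | 0.22 | 0.85 |
| 80% | (0.80 + 0.70 × 0.80)/2 = 68% | 0.07 | 0.51 |

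Over the whole assumed range, P(Go) runs from 0.003 to 0.87 with all randomised and from 0.25 to 0.99 with crossovers removed.

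**A case in the other direction.** With 8/10 intervention women adherent, 3 crossovers and 2 further controls non-adherent for other reasons, the control rate after removal is 5/7 = 71% and the pooled rate 13/17 = 76%. That is not Go, so removal does not guarantee a pass.

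**The case against.** The strongest reply is that the article says where the data go, not which denominator criterion 2 uses. The study sample could mean all 20 women, the sample is fixed at 5 + 5 per country, and the Objective speaks of rates following randomisation. Under that reading there is no bias. Exact denominators may also be set in an analysis plan that is not shown. This stands as far as it goes: exclusion is the natural reading but not the only one. It does not remove the point, because the reclassification is a stated rule and the two readings it allows can give different progression decisions.

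A reader might go further and infer three things that the article does not support.

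- **That control retention is near 100% by construction.** It is not. Controls lost to follow-up or with incomplete questionnaires are not reclassified, and data up to consent withdrawal are retained. Only dropout by crossover is hidden.
- **That control non-adherence cannot be observed at all.** Attendance at the sessions offered is monitored, and controls receive those sessions after the delay. Protocol violations, reasons for non-adherence and views on the delay are also collected, and the advisory board follows deviations and withdrawals. What may be lost is the count of early crossover in criterion 2.
- **That the full trial would need a stated multiple of its sample size.** Simple dilution at 40% crossover gives 1/(1 − 0.4)² = 2.8. The article gives no crossover rate, and a woman may leave at any point in the eight weeks, so the full contrast need not be lost.

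It is also fair to say that Table 1 is offered as suggested criteria and that qualitative findings support the decision. The example of such flexibility, however, concerns a criterion that is missed, not one that is passed wrongly.

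**Conclusion.** The point holds in a limited form and should be fixed. On the natural reading, early crossover is removed from criterion 2 and from the dropout estimate for the full trial, and the control completeness rate is computed only on women who stayed. Criterion 2 can then read Go when adherence among all randomised women is 80% or lower. With ten controls, two or three crossovers are enough if eight or nine intervention women adhere.

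The size rests on assumed crossover and adherence rates and on the exclusion reading; if all 20 women form the denominator, the effect is nil. The primary outcome, consent to randomisation in the control group, is given before any crossover and is unaffected. In a 20-woman pilot whose main question is untouched, this calls for a correction and is not a fundamental flaw.

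**What to change.** Change the analysis rule in the control-group paragraph and refer to it from Table 1:

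- Criteria 2 and 3 and the control-arm rates use all women as randomised; for controls, all who gave the second consent.
- A control who starts the package early counts as non-adherent to allocation in criterion 2 and stays in the denominators for completeness and dropout.
- Her data stay in the control arm as well as being used in the cohort.
- The number of early crossovers and the time from second consent to crossover are reported as results in their own right.

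A woman's right to leave the delay and receive the package is unchanged. The cost is about one sentence of text, with no new data collection. The only downside is that the adherence figure may look less favourable.
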